## Objectives, Hypotheses and Outcomes

**Objective 1:** To establish specific spatiotemporal activation maps for TCSCS at various spinal cord segments known to be involved in LUT and bowel control.

**Hypothesis 1:** In light of recent findings on the efficacy of spinal cord stimulation to improve bowel and LUT function, the optimal setting for motor responses (i.e. mapping) will be revealed during TCSCS.

**Primary outcome 1:** An individualized TCSCS map (i.e. location and stimulation parameters) to elicit optimal skeletal muscle activation corresponding to spinal cord segments involved in LUT and bowel control

**Objective 2:** To test whether targeted short-term TCSCS is safe with respect to cardiovascular consequences (e.g. autonomic dysreflexia) and can repeatedly improve LUT and bowel functions in humans with chronic SCI.

**Objective 2A) LUT function (safety/efficacy):** To test whether targeted short-term TCSCS is safe and can induce detrusor contractions (*voiding function*) while relaxing the EUS, i.e. to avoid DSD and independently enhance EUS tone (*storage function*).

**Hypothesis 2A):** In light of recent findings demonstrating TCSCS improves LUT function, we hypothesize that short-term TCSCS will improve voiding and storage functions without ACVEs.

**Outcome 2A):** Changes from baseline in the following UDS parameters for bladder capacity/compliance:

- i. Volume at the first sensation
- ii. Intravesical pressure (Pves) at the first sensation
- iii. Volume at the leakage point
- iv. Pressure at the leakage point
- v. Maximum bladder volume
- vi. Pves at the maximum bladder volume

**Objective 2B) LUT function (repeatability of TCSCS to improve UDS parameters):** To test whether targeted short-term TCSCS will repeatedly improve UDS parameters across different stimulation sessions.

**Hypothesis 2B):** TCSCS will elicit reproducible improvements in UDS parameters without ACVEs.

**Outcome 2B):** Reproducibility of changes within urodynamic parameters during stimulation will be assessed during two consecutive urodynamic procedures. UDS parameters for bladder capacity/compliance:

- i. Volume at the first sensation
- ii. Pves at the first sensation

**Objective 2C) Bowel function (safety/efficacy):** To test whether targeted short-term TCSCS is safe and can result in an immediate increase in anorectal pressure.

**Hypothesis 2C):** TCSCS will increase anorectal pressure without adverse cardiovascular effects.

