### Statistical Plan

Statistical analysis on LUT, bowel and sexual function will be performed (n = 40 with SCI).

A sample size calculation was performed using G\*power, version 3.0.10, with power set at 0.8 and  $\alpha$  at 0.05. Data from participants that match our inclusion criteria (n = 5, level of lesion C5 – T10, motor-complete AIS, A or B) were used from a recent TCSCS study. A minimum sample of 26 participants is required to detect a significant change in voiding efficiency [voided volume / (voided volume + post-void residual volume)] with short-term TCSCS (stim-off =  $37.8 \pm 40.6\%$  vs. stim-on =  $58.2 \pm 39.4\%$ , effect size = 0.510). Presently, there are no long-term TCSCS data with LUT and bowel outcomes, consistent with those proposed in this protocol, to facilitate a meaningful power calculation. Therefore, given this is a pilot trial study, and in order to account for drop out with long-term TCSCS, we aim to investigate 40 individuals with SCI (n = 40, C5 – T6). Short-term TCSCS effects on UDS parameters (AIM 2A) as well as ARM testing (AIM 2C) with or without different stimulation configurations will be assessed using a repeated measures non-parametric analysis of variance (ANOVA), i.e. Kruskal–Wallis test. Data from the repeatability portion of the study (AIM 2A) will be assessed within (same session) and between (different sessions) visits (2 and 3) using a repeated measures non-parametric ANOVA. TNFBM will also be assessed using a repeated measures non-parametric ANOVA.

Long-term TCSCS: Differences in continuous variables for questionnaire data (NBSS, NBD Score, I-QoL, IIEF-15 or FSFI) in AIM 3 will be assessed using a two-way repeated measures [baseline, immediately post long term TCSCS as well as post-interventional follow up at 6 and 12 weeks] ANOVA comparing changes between moderate and intensive TCSCS. Furthermore, UDS testing as well as 'faecal continence severity' (baseline and end of TCSCS 6-week period) will be assessed using Wilcoxon signed-rank tests within

groups. A P-value less than 0.05 will be considered statistically significant. A complete thematic analysis will be performed to collect contextual qualitative data from the sexual health interview.

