### Urodynamics

Participants will undergo standard clinical procedures for UDS, including cystometry with water at 21°C and a filling rate of < 30 mL per minute through a 6F double lumen catheter with the participants in the supine position. Abdominal pressure will be measured with a 10F intrarectal balloon catheter. Pelvic floor electromyography will be recorded during cystometry with a surface electrode placed on the

perineum. Filling will be stopped when the participants report a sensation of fullness, at the moment of urine leakage, if blood pressure reaches levels of 180/110 mmHg, or per the request of the patient.

Following the standard clinical assessment UDS we will perform UDS with TCSCS. To assess the efficacy of short-term TCSCS' on LUT function, we will first prefill the bladder (i.e. 50-75% of cystometric capacity from the first UDS) without eliciting detrusor overactivity or autonomic dysreflexia. Then, TCSCS (as described above) will be delivered for 60 s each interspersed with 30 s rest (i.e. no stim) to optimize the configuration for each individual. Stimulation frequency and location will be guided by the results of the Baseline EMG Mapping of Spinal Cord Segments performed during visit 3.

TCSCS will be stopped when the participants report a sensation of fullness, at the moment of urine leakage, if blood pressure reaches levels of 180/110 mmHg, or per the request of the patient.

Urodynamics will be performed by a trained clinician (MD or RN) under the supervision of [name] (MD), who is a urologist.

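### Hypothesis 2A rests on six unranked urodynamic parameters and an omnibus test, so the protocol fixes neither the stimulation-on versus off contrast nor the result that decides the claim

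*Protocol*

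**What the plan says.** In the protocol section Objectives, Hypotheses and Outcomes, Hypothesis 2A is a single efficacy claim: "we hypothesize that short-term TCSCS will improve voiding and storage functions without ACVEs". Outcome 2A is given as "Changes from baseline in the following UDS parameters for bladder capacity/compliance", followed by six items: volume and intravesical pressure (Pves) at first sensation, volume and pressure at leakage, and maximum bladder volume with its Pves. None is ranked, none has a stated direction, and no rule says whether one, all or a particular item must change. The protocol uses the word primary only for the mapping outcome and for the incontinence domain of the bladder symptom score in Aim 3A.

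The Statistical Plan says that short-term effects "with or without different stimulation configurations will be assessed using a repeated measures non-parametric analysis of variance (ANOVA), i.e. Kruskal–Wallis test". Its threshold covers every test: "A P-value less than 0.05 will be considered statistically significant". The number of configurations is not given. The Urodynamics section adds that stimulation is delivered in repeated short periods "to optimize the configuration for each individual".

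The sample size uses another variable: "A minimum sample of 26 participants is required to detect a significant change in voiding efficiency", comparing stimulation off with stimulation on at an effect size of 0.510.

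**The concern.** Three things needed to decide Hypothesis 2A are left open.

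- **Contrast.** An omnibus test over off and several configurations asks whether any conditions differ. It can be significant because configurations differ from one another, with no benefit of on over off. Only with exactly two conditions does it reduce to on against off, and the plan speaks of configurations in the plural.
- **Parameter.** With six co-equal outcomes and one limit of 0.05, whichever parameter reaches significance can be put forward as support for 2A.
- **Direction.** Outcome 2A speaks only of change. By contrast, Outcomes 2C and 3A state both a direction and a size (at least 50%).

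The variable used to plan the sample size cannot serve as an implied primary, because it does not appear under Outcome 2A. At stake is whether a reported improvement in bladder function carries the stated 5% error.

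**Working it through.** **1. The plan's own figure.** Inputs from the Statistical Plan: off 37.8 (SD 40.6), on 58.2 (SD 39.4), effect size 0.510, power 0.8, alpha 0.05, n = 26.

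- Difference: 58.2 − 37.8 = 20.4.
- SD of the paired difference, assuming within-person correlation 0.5: √(40.6² + 39.4² − 2 × 0.5 × 40.6 × 39.4) = √1601.1 = 40.0. Then 20.4 / 40.0 = 0.510, as stated. Dividing by the average SD gives the same value, so the correlation cannot be recovered with certainty.
- Paired t-test (noncentral t) at 0.510: one-sided alpha 0.05 gives n = 26 (power 81.2%). Two-sided gives n = 33, and power at 26 is 70.5%.
- Signed-rank test (efficiency 3/π against the t-test): 27 one-sided, 34 two-sided.

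The stated 26 is therefore reproduced as a one-sided paired comparison of voiding efficiency. That is an on-versus-off contrast, but for a variable outside the six.

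**2. Error if any one of six counts.** From the protocol: six parameters, 0.05 each. Assumed, because the protocol is silent: success on any one, equal correlation ρ between the test statistics, and tests of true size 5%.

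- Independent, two-sided: 1 − 0.95⁶ = 0.265.
- Independent, favourable direction only (0.025 each): 1 − 0.975⁶ = 0.141.
- Correlated: Z_j = √ρ·U + √(1 − ρ)·e_j for j = 1 to 6, with U and e_j independent standard normal, 300,000 draws.

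| ρ | any of six, two-sided 0.05 | any of six, favourable only |
|---|---|---|
| 0 | 26.5% | 14.1% |
| 0.3 | 24.1% | 12.1% |
| 0.5 | 20.7% | 10.4% |
| 0.7 | 16.4% | 8.2% |
| 0.9 | 10.9% | 5.5% |

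Simulated paired data (n = 40, ρ = 0.5) analysed by signed-rank tests gave 21%, in agreement.

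**3. The test as named.** Kruskal–Wallis is for independent groups. Applied literally to paired data with two conditions, n = 40 and no effect, the error of a single test was 5.2%, 2.2%, 0.6% and 0.05% at within-person correlations of 0, 0.3, 0.5 and 0.7. Signed-rank stayed between 4.6% and 4.9%. Across six parameters with ρ = 0.5, literal Kruskal–Wallis gave 21% at within-person correlation 0 but about 4% at 0.5.

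**4. After a fix.** One variable and one contrast: 5%. Bonferroni across six: 0.05 / 6 = 0.0083 each, and 1 − (1 − 0.0083)⁶ = 4.9% if independent. Holm also holds the family-wise error at 5% and is never less powerful than Bonferroni.

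**The case against.** The study is described as a pilot and proof of concept, and methods for multiplicity and post-hoc contrasts commonly stand in a statistical analysis plan, which is not at hand. Both points stand. The absence of a Holm or similar rule is not itself the finding, and the pilot label lowers the severity. But which outcome and contrast answer a stated hypothesis is a matter for the protocol. This protocol also fixes a test and a significance limit, gives a power calculation, and does not call 2A exploratory.

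Four stronger readings are tempting and are not supported:

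- **That 2A has a false-positive rate of 21%.** This needs ρ near 0.5, success on any one of six, either direction counting, and a valid paired test. The protocol states none of these, and its named test can be conservative.
- **That comparing each of several configurations with off makes the rate far higher.** The number of configurations compared during urodynamics is not given, so no figure follows.
- **That a rise or a fall in Pves would equally be called success.** The six are labelled as capacity and compliance measures, and the background section wants low pressure during storage. A storage direction can be inferred. It is still not stated, and Objective 2A also seeks induced detrusor contraction.
- **That maximum bladder volume is the obvious deciding parameter.** Under the Urodynamics section, filling may stop at reported fullness or at leakage. The stimulated run begins from a bladder prefilled to 50–75% of the capacity found in the preceding unstimulated test, so the two runs are not like for like. The parameter also covers storage only, while the hypothesis covers voiding as well.

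**Conclusion.** The structural point holds. Hypothesis 2A has six co-equal outcomes without stated direction and an omnibus test that is not the on-versus-off contrast. Its sample size rests on a variable outside the six. This should be corrected, although in a pilot it is not fatal.

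The size is illustrative: about 11% to 26% family-wise error for a valid two-sided paired test, or about 5% to 14% for false improvement only. Both ranges assume success on any one of six and equal correlations from 0.9 down to 0. They do not describe the Kruskal–Wallis test taken literally, which at a within-person correlation of 0.5 gives about 4% across the six. That low rate is no safeguard: it comes from ignoring the pairing, which also costs power.

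**What to change.** In Objectives, Hypotheses and Outcomes and in the Statistical Plan:

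- Make the paired stimulation-on minus stimulation-off contrast the deciding analysis for 2A, by a two-sided Wilcoxon signed-rank test at 0.05. State which stimulated record supplies the on value.
- State the direction of benefit for each parameter.
- Then do one of two things. Either name one deciding variable before data are seen, and label the six exploratory with estimates and confidence intervals; or apply Holm across the six. Voiding efficiency is the natural deciding variable, since the sample size is built on it, and it should then be added to Outcome 2A.
- Label the across-configuration omnibus test exploratory, and use a repeated-measures test such as Friedman.

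Cost: mainly wording. At the plan's effect size, a two-sided signed-rank test needs 34 participants. The planned 40 cover this with up to 6 losses (40 − 34), so no participants are added. If voiding efficiency is chosen, the Urodynamics section should say that voided and residual volumes are recorded with and without stimulation, which it does not now describe. The downside is that an isolated P below 0.05 on one parameter can no longer be called a positive result for 2A.

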### *Procedures*

#### *TCSCS*

TCSCS will be delivered using a non-invasive central nervous system stimulator (TESCoN, SpineX Inc., CA, USA). A self adhesive round electrode placed on the skin between spinous processes at the midline over the vertebral column will function as a cathode, and two rectangular self-adhesive electrodes located

symmetrically on the skin over the iliac crests as anodes. To activate the spinal circuits known to be involved in LUT and bowel control (AIM 1), TCSCS will be delivered individually between spinous processes T10-11, T11-12, T12-L1, and L1-L2 (conus medullaris). Stimulation will be applied at various frequencies ranging between 1Hz and 90Hz. Current amplitude will start at 10mA and will be increased in incremental steps until tolerable or until responses plateau. Specific areas for electrode placement will be examined and prepared to reduce skin impedance. A temperature probe will be positioned adjacent to the cathode in order to monitor changes in skin temperature to prevent potential skin damage. TCSCS will be delivered under the supervision of either [name] or [name], who are both Physical Medicine and Rehabilitation physicians.

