### Surface EMG

EMG signals will be recorded using a commercially available Delsys system and custom LabVIEW software (LabVIEW, National Instruments, USA). EMG data will be analyzed offline using custom MATLAB routines (MathWorks, Natick, USA). EMG signals will be sampled at 10KHz, bandpass filtered (5Hz-5KHz) and rectified for analysis. Potential motor targets and muscles we will record from include: T10-12= lower abdominal [rectus abdominis], L1-2= hip flexor [rectus femoris], L3= knee extensors [vastus medialis and lateralis], L4= ankle dorsiflexors (tibialis anterior), L5= long toe extensor [hallucis longus], S1= ankle plantar flexors [gastrocnemius], S2-3= knee flexion (hamstring), S2-S4 perineum (only control participants). Parameters of interest will be rectified surface EMG, time-locked to the electrical stimulation in 300 us bins. Motor evoked potential latency and amplitude will be recorded if present. Surface EMG will be recorded under the supervision of either [name] or [name], who are both Physical Medicine and Rehabilitation physicians.

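### The urodynamic pressure outcomes in 2A and 2B are intravesical pressure or unnamed, never detrusor pressure, so a change under stimulation cannot be attributed to the bladder

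*Protocol*

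**What the plan says.** In the Protocol, section Objectives, Hypotheses and Outcomes, Objective 2A asks whether short-term stimulation can make the detrusor contract while the external sphincter relaxes, and separately whether it can raise sphincter tone. Outcome 2A is then defined as "Changes from baseline in the following UDS parameters for bladder capacity/compliance". Its three pressure items are "Intravesical pressure (Pves) at the first sensation", "Pressure at the leakage point" and "Pves at the maximum bladder volume". Outcome 2B has one pressure item, again Pves at first sensation. The remaining items in both lists are volumes.

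The Urodynamics section provides for the second signal: "Abdominal pressure will be measured with a 10F intrarectal balloon catheter". No section says that this signal is subtracted from Pves or used in an outcome.

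On the intervention, the TCSCS section states that "TCSCS will be delivered individually between spinous processes T10-11, T11-12, T12-L1, and L1-L2". The Surface EMG section lists potential motor targets and recording muscles, including "T10-12= lower abdominal [rectus abdominis]". The Urodynamics section lets the Visit 3 EMG map guide stimulation location and frequency. It has no rule about sites that also activate the abdominal wall.

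**The concern.** A pressure transducer in the bladder reads the detrusor plus whatever the abdomen adds. In an ordinary filling study the abdominal part is nuisance noise. Here it may be caused by the treatment, because the electrodes lie over the lower thoracic and upper lumbar spine. Any abdominal response would then be present with stimulation on and absent with it off. That is a bias in the contrast of interest, and more participants would not average it out.

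An abdominal rise could be read as a detrusor contraction or as a loss of compliance, and it could hide a true fall in detrusor pressure. Repetition, which is the subject of Outcome 2B, gives no protection: an abdominal response that recurs at each session would look like a reproducible bladder effect.

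This is more than a detail left to a later analysis plan. The protocol names the measured variable, and an analysis plan that follows it would analyse Pves.

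**Working it through.** **1. Which pressure each item uses**

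| Item | Pressure named |
|---|---|
| 2A-ii, first sensation | Pves |
| 2A-iv, leakage point | none |
| 2A-vi, maximum volume | Pves |
| 2B-ii, first sensation | Pves |

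Three of four are explicitly Pves, one is undefined, and none is Pdet. Items 2A-i, iii and v and 2B-i are volumes and are outside this point.

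**2. What a change in Pves can mean**

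The standard urodynamic identity, which the protocol does not state, is Pves = Pdet + Pabd. Hence change in Pves = change in Pdet + change in Pabd. With assumed values in cmH2O:

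| Change in Pdet | Change in Pabd | Change in Pves |
|---|---|---|
| 0 | +5 | +5 |
| 0 | +10 | +10 |
| +10 | 0 | +10 |
| +5 | +5 | +10 |

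The last three rows give the same outcome under the plan as written. They differ in Pdet: 0, +10 and +5.

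**3. Scale, as illustration only**

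The protocol reports no pressures, so there is no plan figure to reproduce. Its only sample-size calculation concerns voiding efficiency and does not bear on this point. Assume 40 participants, no detrusor effect, normally distributed within-person changes in Pves, and a two-sided Wilcoxon signed-rank test at 0.05. Simulated proportion of trials declared significant:

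| SD of change | Abdominal rise 0 | 2 | 5 | 10 |
|---|---|---|---|---|
| 10 | about 5% | 22-24% | 85% | 100% |
| 15 | about 5% | 13% | 53% | 98% |
| 20 | about 5% | 9-11% | 33-34% | 85-86% |

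Ranges cover separate simulation runs. These figures are simply the power of a test against an assumed shift. They show what a shift of that size would do, not that it occurs. The Statistical Plan names Kruskal-Wallis for this aim, so the test is also a stand-in for a paired contrast.

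**4. Compliance**

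Assume 300 mL stored for a 15 cmH2O rise: 300/15 = 20 mL/cmH2O. If abdominal pressure adds 5 only at the end of filling, the result is 300/(15 + 5) = 15. If it adds 10, it is 300/(15 + 10) = 12. If the same amount is added at both ends, the rise stays 15 and compliance stays 20. The protocol gives no compliance formula, so either case is open.

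**5. Does the subtraction introduce a problem of its own?**

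Pabd is taken from a rectal balloon, and Hypothesis 2C expects stimulation to raise anorectal pressure. Suppose the true changes in Pdet and Pabd are both 0 but the balloon reads +10 from a local rectal effect. Calculated Pdet then changes by 0 - 10 = -10, a false fall. Suppose instead that Pdet truly rises by 10 and the balloon again reads +10. Calculated Pdet changes by 10 - 10 = 0, and a true contraction is hidden. The first case is recognisable if all three signals are shown, because Pabd rises while Pves does not. The second gives the same triple (Pves +10, Pabd +10, Pdet 0) as a pure abdominal contraction, so the pressures alone cannot separate those two.

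**The case against.** Four objections carry weight.

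- **Abdominal recruitment is not shown.** The stimulation sites are spinous-process interspaces, and the protocol labels L1-L2 as the conus. The muscle list appears to run by cord segment, down to S2-S4. The two scales do not coincide, and rectus abdominis is only a potential target. A reader might infer that the protocol expects stimulation to contract the abdominal wall; the text does not support that. This stands, and it limits the claim to what could happen.
- **Pves has a stated rationale.** The Background literature review treats high intravesical pressure as the source of harm to the urinary tract and calls for restoring function with respect to intravesical and abdominal pressure. This stands. It is a reason to keep Pves, but it does not turn Pves into a measure of detrusor contraction.
- **Subtraction is imperfect,** for the rectal-balloon reason in step 5. This stands, and it rules out replacing Pves by Pdet and showing nothing else.
- **Both channels are kept in a proof-of-concept study powered on voiding efficiency,** so Pdet can always be derived later. It can, but if the protocol names Pves, a switch to Pdet once results are known would be a change of outcome after the fact.

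A reader might also infer that every pressure outcome is Pves. The leakage item does not name its pressure, so the documents support three of four.

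**Conclusion.** The point holds in this form: the plan's pressure outcomes cannot separate a bladder effect from an abdominal one, and the leakage item is undefined. The defect lies in the outcome definition, not in the measurement, since the abdominal signal is already collected. The conclusion rests on the standard identity for Pves and on the absence of Pdet from every outcome. It does not require that stimulation actually contracts the abdominal wall.

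The size cannot be taken from the documents. Any abdominal change passes into Pves one for one, but how large it would be, or whether it arises at all, is not given. The simulated percentages should not be read as this trial's false-positive risk, nor the values 15 and 12 mL/cmH2O as expected compliance losses. The volume items are unaffected.

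**What to change.** In Outcome 2A (ii, iv, vi) and Outcome 2B (ii), specify detrusor pressure, Pdet = Pves - Pabd, as the measure on which detrusor and compliance conclusions rest. For item iv, name the pressure explicitly. State that any compliance value is computed from Pdet.

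Keep Pves, and report Pves, Pabd and Pdet together with stimulation on and off. An abdominal contraction, or a stimulation effect on the rectal balloon, then has a chance of being seen. Where Pves and Pabd rise together and Pdet does not change, state that the pressures alone do not settle the source.

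The cost is a wording change before the data are examined and slightly more analysis; no new measurement is needed. The downside is that Pdet inherits any artefact in the rectal channel, which is why all three signals should be shown.

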**Outcome 2C):** Mean increase in maximum resting pressure by at least 50%.

**Objective 3) LUT, bowel and sexual functions (long-term TCSCS):** To test whether targeted long-term TCSCS (6-week trial) is safe and can improve urinary and faecal continence in humans with chronic SCI.

**Objective 3A)** To test whether targeted long-term TCSCS can improve urinary and faecal continence.

**Hypothesis 3A)** Long-term TCSCS will improve urinary and faecal continence. These improvements will be greater in individuals who complete intensive long term TCSCS compared to individuals who complete moderate long term TCSCS.

**Outcome 3A):** Mean decrease in the frequency of urinary and faecal incontinence by at least 50%.

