**Objective 3B) To test whether targeted long-term TCSCS can improve sexual function.**

**Hypothesis 3B:** Long-term TCSCS will improve sexual function in male and female participants, with an emphasis on overall sex life satisfaction. These improvements will be greater in individuals who complete intensive long term TCSCS compared to individuals who complete moderate long term TCSCS.

**Outcome 3B:** Mean improvement in satisfaction with participant's overall sexual life.

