### Research design

This is a proof of concept study to demonstrate the clinical efficacy of real-time (short-term) TCSCS (proof-of-concept) to improve LUT, and bowel in adults with chronic SCI. This is also a pilot trial phase and a proof-of-concept study to test clinical long term efficacy of TCSCS to improve LUT, bowel and sexual function in adults with chronic SCI.

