### *Visits 7 – 18 or 36: Long Term TCSCS – Weeks 7-12:*

Approximately 90 minutes per visit.

Participants will come to ICORD for long term TCSCS, either 2 days/week (moderate) or 5 days/week (intense) for 6 weeks for a total of either 12 sessions or 30 sessions. Please see Description of Assessments for the details of an individual session.

During the 6 weeks of long term TCSCS, TNFBM will be measured during participants' conventional bowel routines at home. Participants will be asked to record the time from 'suppository insertion' to 'when bowel evacuation is completed' once per week for the bowel movement completed mid-week during each week of the 6 week TCSCS pathway.

24 ABPM will be performed mid-way through the 6 weeks and during the final week of the 6 weeks of treatment in combination with the participants' bowel routine.

## Visit 19-20 OR 37 – 38: Immediate Post-TCSCS Assessments – Week : 13

Visit 19 or 37 (approximately 3 hours):

After the 6 weeks of TCSCS, all participants will complete 1 visit at ICORD including UDS assessments and a SCI severity assessment (ISNCSCI). Please see description of Assessments for details.

Visit 20 or 38 (approximately 1 hour):

A series of questionnaires on low urinary tract function, bowel function, cardiovascular function and sexual health will be conducted by telephone or video conference call (considering the present COVID-19 pandemic environment). The questionnaires are listed below and details can be found in the Description of Assessments Section.

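### The long-term phase says it tests whether TCSCS improves continence and sexual function, but both arms are stimulated, so the planned analyses can show only uncontrolled change and a dose difference

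*Protocol*

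**What the plan says.** **The claim.** In the Objectives, Hypotheses and Outcomes section, Objective 3A is "To test whether targeted long-term TCSCS can improve urinary and faecal continence" and Objective 3B is "To test whether targeted long-term TCSCS can improve sexual function". Hypotheses 3A and 3B each contain two statements: that long-term TCSCS will improve the outcome, and that intensive stimulation will improve it more than moderate. The Research design section describes this phase as a pilot and proof of concept "to test clinical long term efficacy of TCSCS to improve LUT, bowel and sexual function in adults with chronic SCI".

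**The success criteria.** Outcome 3A is "Mean decrease in the frequency of urinary and faecal incontinence by at least 50" percent. Outcome 3B is "Mean improvement in satisfaction with participant's overall sexual life". Neither names a comparator.

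**The arms.** Under Long Term TCSCS, Weeks 7-12, participants attend "either 2 days/week (moderate) or 5 days/week (intense) for 6 weeks for a total of either 12 sessions or 30 sessions". No sham, untreated or delayed-start group is described. The control participants mentioned under Surface EMG and under Remuneration are not given any long-term role.

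**The analysis.** The Statistical Plan assigns the questionnaires (NBSS, NBD Score, I-QoL, IIEF-15 or FSFI) to a two-way repeated-measures "ANOVA comparing changes between moderate and intensive TCSCS", over baseline, end of treatment and the 6- and 12-week follow-ups. Urodynamics and faecal continence severity, at baseline and at the end of the 6 weeks, "will be assessed using Wilcoxon signed-rank tests within" groups. The threshold is P<0.05.

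**The concern.** The first statement in each hypothesis needs a comparison with no stimulation, and the long-term phase has none. It can then be judged only by change from baseline. Such change mixes any effect of TCSCS with expectation, regular supervised contact and repeated questionnaires. Most of the outcomes for Objective 3 are self-reported, including the NBSS incontinence domain that the protocol labels primary for this aim, and no blinding is described.

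The dose contrast cannot fill the gap. It is zero if both doses work equally well and also zero if neither works.

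The plan could therefore mislead in both directions. Non-specific improvement could be reported as efficacy at P<0.05, and a real effect of equal size in both arms would give a null result in the only between-arm comparison.

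**Working it through.** **1. The plan's own figure.** The protocol gives one sample-size figure, 26, for short-term voiding efficiency. The effect size is (58.2 − 37.8) / √((40.6² + 39.4²)/2) = 20.4 / 40.0 = 0.510. With α = 0.05 and power 0.80, a paired t-test needs 26 if one-sided (power 0.812) and 33 if two-sided, so 26 reproduces as a one-sided paired calculation. It concerns stimulation on versus off in the short-term phase and supports nothing in Objective 3. The protocol says that no data existed for a long-term power calculation.

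**2. Which analysis answers which claim.**

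| Claim | Comparator needed | What the plan offers |
|---|---|---|
| TCSCS improves the outcome | No stimulation | Change from baseline only: within-group Wilcoxon tests (urodynamics, faecal continence severity) and, for the questionnaires, whatever the ANOVA shows over time |
| Intensive is better than moderate | The other dose | ANOVA between arms, questionnaires only |

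The first row has no concurrent comparator for any endpoint.

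**3. Illustration of the within-group test.** Assumptions, none of them in the protocol: no true TCSCS effect; 20 per arm (no split of the 40 is given); normally distributed changes; a two-sided test (sidedness is not stated); a non-specific shift of δ SD of the change score. For a paired t-test the rejection probability comes from the noncentral t distribution with 19 degrees of freedom and noncentrality δ√20. The Wilcoxon signed-rank test was simulated with 4,000 replicates.

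| δ | δ√20 | Paired t, n = 20 | Wilcoxon, n = 20 |
|---|---|---|---|
| 0 | 0 | 0.050 | 0.049 |
| 0.2 | 0.894 | 0.136 | 0.126 |
| 0.3 | 1.342 | 0.247 | 0.243 |
| 0.5 | 2.236 | 0.565 | 0.545 |

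A second simulation with 10,000 replicates gave 0.238 at 0.3 SD and 0.536 at 0.5 SD. When two groups of 20 share the same shift, a between-group t-test stays near nominal: 0.050, 0.054 and 0.048 at shifts of 0, 0.3 and 0.5 SD.

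**4. Relation to the 50% criterion.** Let M be the baseline mean frequency. An expected shift of δ SD equals a 50% fall only if δ × SD = 0.5M, so SD = 0.5M/δ. At δ = 0.5 the SD of change must equal M, and at δ = 0.2 it must be 2.5M. The rates in step 3 are therefore rates of P<0.05 and do not give the chance of meeting Outcome 3A.

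**5. What the dose contrast can carry.** At 20 per arm, a two-sided t-test has noncentrality d√(20/2). At d = 0.5 this is 1.581, with power 0.34; at d = 0.8 power is 0.69. For 80% power at d = 0.5 the normal approximation gives 2(1.960 + 0.842)²/0.5² = 62.8, so 63 per arm. The arms also differ in contact: 30/12 = 2.5 times the sessions. At about 90 minutes each, that is 45 hours against 18.

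**The case against.** **A between-arm test is planned.** A reader might infer that improvement is tested only against baseline throughout. That is not so: the questionnaire ANOVA compares the doses and matches the second sentence of Hypotheses 3A and 3B. What stands is that it does not address the first sentence.

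**The Wilcoxon tests are not assigned to the questionnaires.** This is correct. They cover urodynamics and faecal continence severity, so the rates in step 3 cannot be carried over to the NBSS or IIEF-15. Urodynamics is instrumented, which weakens the expectation argument there. It does not remove it, since first-sensation volumes and the stopping of filling depend partly on what the participant reports.

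**A pooled pre-post test on all 40 would reject more often.** The plan states no such test and does not say that the ANOVA time effect will be read as efficacy. No figure for it is relied on here.

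**The sizing uses a stimulation-off condition.** A reader might take this as the comparator intended for Objective 3. It belongs to the short-term phase and says nothing about the long-term one.

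**Participants are stable.** Injury more than a year old, medication stable for 4 weeks and stable management of related problems limit natural recovery and co-treatment change. They do not limit expectation, contact or repeat-questionnaire effects.

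**It is a pilot, and an analysis plan may add detail.** Pilot status justifies having no control arm and no long-term power calculation, so the documents do not support a demand for a sham arm. It does not justify calling uncontrolled change a test of efficacy. That mismatch lies among the protocol's own objectives, arms and named tests, and an analysis plan cannot supply an unstimulated comparator.

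**Conclusion.** The point holds as a mismatch between claim and comparator. The protocol says that the long-term phase tests whether TCSCS improves continence and sexual function, while its arms and analyses can deliver only uncontrolled change and a comparison of two doses. Neither a within-group P<0.05 nor a 50% mean decrease would separate TCSCS from non-specific change.

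Under the assumptions in step 3, a within-group Wilcoxon test would be significant in about 13%, 24% and 55% of trials at shifts of 0.2, 0.3 and 0.5 SD, against a nominal 5%. The logical gap does not depend on these figures. Their size rests wholly on the assumed shift, for which the protocol gives no value, and on the assumed 20 per arm.

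A reader might go further and conclude that the design is invalid, or that the dose contrast could simply replace the efficacy claim. The first does not follow for a declared pilot. The second fails because the contrast has low power, is confounded with clinic contact, and has no stated method of allocation: the randomised step in the protocol covers only the order of urodynamics and manometry.

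**What to change.** Change the wording in three places and add one interpretation rule.

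1. In Objective 3 and the first sentence of Hypotheses 3A and 3B, restate the aim as estimating change from baseline during long-term TCSCS, together with an exploratory moderate-versus-intensive comparison.
2. In the Research design section, replace the long-term efficacy wording in the same way.
3. In the Statistical Plan, report within-arm changes as estimates with 95% confidence intervals, labelled uncontrolled. This includes the percentage decrease in Outcome 3A. State that neither their P-values nor the ANOVA time effect will be read as evidence of efficacy.
4. State that a null dose contrast does not show lack of effect, and that a positive one is confounded with the 2.5-fold difference in clinic contact.

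This adds no participants, visits or procedures. The cost is that the long-term phase gives up its stand-alone efficacy claim. What remains between arms is a comparison with power of about 0.34 at d = 0.5 (20 per arm assumed), which is why it should be called exploratory.
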